## Discussion

This multi-centre, stepped-wedge controlled study will provide peer support to people seeking care for mental health conditions within general practice. This will be achieved by connecting participants with peer workers, with the intention of improving access to relevant supports, improved self-efficacy in navigating the mental healthcare system, taking control of their own health needs, mitigating psychological distress, and promoting personal recovery. Aligned with the EBCD ethos, the ongoing engagement with various key stakeholder groups will provide opportunities for continuous improvement, monitoring, and maintenance of the intervention and its outcomes.

The study may also further benefit the family members and carers involved in the participant’s care by reducing the amount of support they provide. In addition, peer workers may experience increased self-efficacy, along with greater understanding of general practice, from providing support through this intervention. Furthermore, practice staff may benefit from a greater understanding and acceptance of the peer worker role through exposure to peer worker care processes. The results of this study will provide greater insight into the role of for peer workers within the primary care setting. Finally, findings around the cost–benefit of the PS-PC will inform economic feasibility of peer workers in primary care settings. There is a compelling need for a comprehensive trial of peer support at the primary level [3]. If positive, the study may provide information to support the inclusion of primary mental health peer workers within the Medicare Benefits Schedule. If negative, this adequately powered study will help to inform practice within CMOs and clinical practice. Overall, this study will provide opportunities to extend the role of peer workers throughout the healthcare system.

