## Sample size

The sample size calculation (*n* = 264 participants; 66 per practice) is based on the primary outcome of the self-efficacy score from an RCT assessing the effectiveness of peer support for mental health outpatients in Germany [29]. Adjusted scores significantly improved by an average of 1.77 points (95% CI 0.02–3.53) in the peer support group compared to usual care (mean score = 24.3, pooled SD = 7.2) in the 6-month follow-up. As this study is based on 9-month follow-up, the upper confidence level of the improved score will be used. Assuming a 10% attrition rate, we will need to recruit 66 participants per practice with a total of 264 participants. This achieves at least 80% power to detect a difference of mean self-efficacy score of 3.53 points. A power and sample-size analysis for hypothesis test from Stata version 16.1 was used to calculate the sample size*.* The test statistic used is the one-sided Wald *Z*-test and the significance level of the test is 0.05. Assuming heterogeneity amongst practices and substantial differences (i.e., minimal resemblance) in participants at each site, the responses of participants will not be significantly influenced by their enrolment at a particular practice. As such, the ICC is 0.01.

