## Statistical methods

Independent sample *t*-test and standard Chi-square test for association with continuity correction will compare participant characteristics during usual care with those during mid- and post-intervention. Multivariate multilevel mixed-effects models will be used to examine changes in outcome measures between pre-intervention baseline and post-intervention follow-up over time (6, 12, and 18 months) including interactions between pre-intervention baseline and post-intervention follow-up over time. The comparison between care as usual (baseline) and post-intervention (3-months post-baseline) will be of primary importance, whilst subsequent time points will inform the longevity of any intervention-related effects. This analytical strategy is selected due to the hierarchical nature of the data, where participants are nested within practices. Linear models will be used for continuous outcomes (i.e., GSE, K10, RAS-DS, YES, EQ-5D-5L, TFA) and logit models for binary outcomes (e.g., demographics, diagnosis, etc.). The two-sided test will be performed for all analyses, 95% confidence interval reported, and level of significance set at *p* < 0.05. All analyses will be performed using Stata software version 16.1 and R version 4.1.1. Responses on the EQ-5D-5L integrated with survival curves will be integrated estimate quality adjusted life years using the quality-adjusted survival analysis method. Participant self-reported service use during usual care will be compared with those during and post-intervention to determine within-trial incremental costs and trial effectiveness. Where there is missing data, intention-to-treat protocol will be followed for all participants who receive peer support, where baseline information is available. If there is a significant amount of missing data (missing at random), multiple imputation will be used.

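### The adequate-power label that is meant to make a negative result informative is not supported by the protocol's own figures: about 70% two-sided power at 3.53 points and about 24% at 1.77

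*Protocol article*

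**What the plan says.** The Discussion of the protocol article first gives a use for a positive trial (supporting inclusion of primary mental health peer workers in the Medicare Benefits Schedule). It then gives one for a negative trial: "If negative, this adequately powered study will help to inform practice within CMOs and clinical practice".

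The power behind that sentence is set out under Sample size. The reference is an earlier randomised trial of peer support in outpatients: "Adjusted scores significantly improved by an average of 1.77 points (95% CI 0.02–3.53) in the peer support group compared to usual care", with a pooled SD of 7.2. The planning difference is not that estimate: "As this study is based on 9-month follow-up, the upper confidence level of the improved score will be used". The claim is then: "This achieves at least 80% power to detect a difference of mean self-efficacy score of 3.53 points". The test assumed is given as: "The test statistic used is the one-sided Wald *Z*-test and the significance level of the test is 0.05". The ICC is 0.01, attrition is 10%, and recruitment is 66 per practice, 264 in all.

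Statistical methods fixes the analysis differently: "The two-sided test will be performed for all analyses, 95% confidence interval reported, and level of significance set at *p* < 0.05". Negative is not defined anywhere in the article, and no rule connects the reading of a null result to the confidence interval.

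**The concern.** In the Discussion sentence, adequate power is the ground on which a negative result is said to inform practice. Power can carry that weight only if the trial would probably have detected an effect worth having. Here the stated power refers to a difference twice the one actually observed in the reference trial (3.53 / 1.77 = 2.0) and to a more lenient test than the one planned. The reason given for using 3.53 is 9-month follow-up, whereas Primary outcome measures and Statistical methods give priority to the comparison at 3 months.

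If peer support worked as well as it did in the reference trial, this trial would more often than not miss it at the planned significance level. A reader who relied on the label could then give a null result more weight than its precision allows.

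**Working it through.** **Inputs.** Sample size section: SD 7.2; ICC 0.01; difference 3.53; reference estimate 1.77; one-sided alpha 0.05; power 80%; attrition 10%; 66 per practice; four practices. Statistical methods: two-sided alpha 0.05 and 95% confidence intervals. My assumption: one practice crosses over per step, giving 5 periods, with different participants measured in each period.

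**1. Reproduce the stated sample size.** The standard stepped-wedge variance (Hussey and Hughes) for I practices and T periods is

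Var = I·s²·(s² + T·t²) / [(I·U − W)·s² + (U² + I·T·U − T·W − I·V)·t²],

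where t² = ICC × SD² and s² = (1 − ICC) × SD² / m, with m participants per practice-period. U is the number of treated practice-periods, W the sum over periods of the squared number of treated practices, and V the sum over practices of the squared number of treated periods.

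- I = 4, T = 5: U = 4+3+2+1 = 10; W = 0+1+4+9+16 = 30; V = 16+9+4+1 = 30.
- 60 completers per practice gives m = 12. Then t² = 0.01 × 51.84 = 0.5184 and s² = 0.99 × 51.84 / 12 = 4.2768.
- Numerator: 4 × 4.2768 × (4.2768 + 5 × 0.5184) = 117.5. Denominator: 10 × 4.2768 + 30 × 0.5184 = 58.32.
- Var = 2.015, so SE = 1.419.
- One-sided power at 3.53: Φ(3.53/1.419 − 1.645) = 80.0%.
- Attrition: 60 × 1.1 = 66 (or 60/0.9 = 67).

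The stated 66 per practice is therefore reproduced. Solving the power statement directly gives the same SE: 3.53 / (1.645 + 0.842) = 1.42.

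**2. Apply the planned two-sided test.** With 66 × 0.9 = 59.4 completers per practice, SE = 1.426.

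| True difference | One-sided 5% | Two-sided 5% |
|---|---|---|
| 3.53 | 79.7% | 69.7% |
| 1.77 | 34.3% | 23.6% |

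Without any attrition (SE 1.361), two-sided power is 73.7% and 25.5%. The difference detectable with 80% two-sided power is (1.96 + 0.842) × 1.426 = about 4.0 points.

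**3. What a non-significant result would exclude.** The 95% half-width is 1.96 × 1.42 = about 2.8 points.

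- An estimate of exactly 0 gives an interval of about −2.8 to +2.8, which includes 1.77.
- To exclude 1.77 the estimate must be below 1.77 − 2.78 = about −1.0.
- To exclude 3.53 it must be below 3.53 − 2.78 = about 0.75.
- If the truth is 1.77, about 76% of trials are non-significant, and about 97% of those have an interval that includes 1.77.
- If the truth is 0, the upper limit falls below 1.77 with probability Φ(−1.01/1.42) = 24%. Removing the 2.5% that are significant in the wrong direction leaves about 21%, that is 21/95 = 22% of non-significant results. The other 78% would not exclude 1.77.

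**4. Sensitivity.** At 59.4 completers per practice, two-sided, ICC values from 0 to 0.10 give 76% down to 62% power at 3.53, and 27% down to 21% at 1.77. If the claim of at least 80% is taken as 90% one-sided, SE = 3.53 / (1.645 + 1.282) = 1.206, and two-sided power at 1.77 is still only about 31%. These are normal approximations that ignore the small-sample penalty of having four clusters, which favours the plan.

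**The case against.** **The sentence is mild.** A reader might infer that failing to reach p < 0.05 would be taken as evidence that peer support does not work. The documents do not support that. The article never equates negative with non-significant, says only that such a result would help to inform practice, and closes the same paragraph by expecting to extend the peer-worker role. This objection stands, and the point is limited to the power label.

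**Intervals are planned and no margin is required.** Statistical methods commits to 95% confidence intervals, and the qualitative findings are also to inform interpretation. A superiority trial needs no pre-set margin, and rules for reading a null interval are commonly left to an analysis plan, which is not shown here. This stands too: the missing margin is not an error in itself. It does not rescue a label that the article states and that its own figures contradict.

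**Any trial is weak at half its design effect.** True, and under the one-sided test the miss rate at 3.53 is the conventional 20%. But the planned test is two-sided, and the half effect here is the only estimate of benefit the article cites.

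**The primary contrast may be more precise.** The article gives priority to baseline versus 3 months. As a plain within-person contrast, SE = 7.2 × √(2(1 − r)/238). With an assumed correlation r of 0 to 0.7 and no clustering or time effect, two-sided power at 1.77 is about 77% to over 99%. The figures in the working do not apply to that contrast. It has no concurrent control, however, and it is not the basis of the stated power, so it cannot justify the label.

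**Conclusion.** The point holds as a wrongly stated property. The trial is described as adequately powered in the sentence that makes a negative result informative, yet under the planned two-sided test the design behind the stated sample size has about 70% power for the optimistic 3.53 points and about 24% for the 1.77 points actually reported. Its interval, about ±2.8 points, excludes 1.77 only when the estimate is about −1.0 or lower.

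This rests on the stepped-wedge comparison that reproduces 66 per practice (one practice per step, five periods, SD 7.2, ICC 0.01) and is stable across ICC values from 0 to 0.10. It does not show that the investigators intend to read a null result as no effect, nor that a margin had to be set in this article.

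**What to change.** In the Discussion, delete the words that call the study adequately powered, or replace them with the actual figures: about 70% two-sided (80% one-sided) power for 3.53 points, and about 24% two-sided power for 1.77 points.

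Add one sentence there and in Statistical methods, for example: *A non-significant primary result will be interpreted from the 95% confidence interval for the GSE difference, and will be reported as inconclusive where that interval still includes a benefit of the size seen in the reference trial (1.77 points).*

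Do not use 3.53 as the margin for concluding that worthwhile benefit is absent. An estimate of 0.7 has an interval of about −2.1 to 3.5, so such a rule would dismiss benefit while 1.77 is well inside the interval.

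The cost is a few words of text; the interval is already planned, and no further data or participants are needed. The price is in the conclusions: most null results would have to be reported as inconclusive, about 78% of them even if the true effect were zero. Restoring 80% two-sided power instead would need about 88 recruited per practice for 3.53 points (79 completers / 0.9) and about 419 for 1.77 (377 / 0.9), which is why correcting the wording is the proportionate step.

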## Trial status

Protocol v1, finalised on 16/10/2023. Recruitment began 9/11/2023. Approximate anticipated date of recruitment completion 25/08/2025.

## Data Availability

Final trial dataset will be retained by Flinders University in South Australia. Access is limited to the investigators involved in the data management of this study ([name]) due to ethical restrictions on data sharing and the sensitivity of data collected. A copy of the data management procedures is available on request. Findings will be disseminated through publication. This may include peer-reviewed journals, government white papers, presentations to sector leaders, and summaries provided to community stakeholder groups. Authorship will be decided on a case-by-case basis. Ethical approval has not been obtained to make data available to the public.

## Abbreviations

PS-PC: Lived experience Peer Support intervention for mental health service consumers in Primary Care
LE: Lived experience
RCT: Randomised control trial
GP: General practitioner
EBCD: Experience Based Co-Design
CFIR: Consolidated Framework for Implementation Research
RE-AIM: Reach, Effectiveness, Adoption, Implementation, Maintenance
CMO: Community-managed organisation
K10: Kessler psychological distress scale
GSE: Generalised Self-Efficacy scale
RAS-DS: Recovery Assessment Scale—Domains and Stages scale
YES-sf: Your Experience of Service scale
EQ-5D-5L: European Quality of Life—Five Dimension, Five Level scale
BSFC-s: Burden Scale for Family Caregivers short scale
TFA: Theoretical Framework of Acceptability
PRG: Project Reference Group
SRG: Stakeholder Reference Group
